#### Diet

The recommended diet will be consistent with the *Dietary Guidelines for Americans 2010* document [20]. Emphasis will be placed on restricting fatty foods and consuming more fruits and vegetables. Total recommended daily caloric intake will be consistent with recommended degrees of weight reduction, based on a graded reduction in total daily caloric intake adjusted to meet goals and avoid rapid weight loss. Each participant will receive a personalized diet plan based on their food diary.

#### Physical activity

The goal will be to increase physical activity levels, reduce sedentary behaviors, and encourage participation in a strength training program. The physical activity program will be based on the patients’ preference and goals. In a graded fashion, we will encourage participants to achieve recommended physical activity guidelines, which will include a strength training program of major muscle groups.

#### Sleep

The sleep component will address recommended sleep duration, the process and stages of sleep, benefits of sleep, and the relationship of sleep to hunger, stress, fatigue, and obesity. Good sleep hygiene and barriers to adequate sleep will be discussed. Strategies will include minimizing procrastination, regularizing a sleep schedule, learning the components of stimulus control therapy, and relaxation strategies.

#### Symptom management

Kate Lorig’s self-management framework [21] will be used to guide the symptom management component. The overall goal of this component will be to provide specific strategies on managing symptoms and to teach participants the necessary skill set to incorporate these strategies into their lives. We will focus on teaching skills related to managing emotions, communicating with caregivers, and managing fatigue (for example, taking rest breaks and re-organizing work spaces) and pain (for example, visualization and breathing exercises).

#### Contact-control intervention

In contrast to the SystemCHANGE™ arm, participants assigned to the information-only group will receive pamphlets that contain information on healthy eating, physical activity, sleep, and symptom management, and will be telephoned at the same time points as the SystemCHANGE™ sessions. These 20-min phone calls are intended to teach participants recommended guidelines for engaging in healthy behaviors and reducing cardiovascular risk. However, the skills taught in the SystemCHANGE™ intervention (for example, identifying a chain of steps/events that comprise the system in which the desired change is to occur) will not be taught in the control intervention. Thus, we will be able to determine whether it is the skills taught in the SystemCHANGE™ intervention or simply the learning of guidelines that promotes engagement in healthy behaviors. Furthermore, the phone calls in the contact-control intervention will provide an equivalent number of contacts with the health education specialist as in the SystemCHANGE™ intervention. Thus, we will be able to determine whether it is the skills taught in the SystemCHANGE™ intervention or simply the interactions with the health education specialist and creating accountability that promotes engagement in healthy behaviors.

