### Interventions

#### SystemCHANGE™

The SystemCHANGE™ intervention will be delivered over a 6-month period involving 12 face-to-face group sessions (1.5 h each) held weekly for 3 months, followed by 3-monthly ‘booster calls’. Intervention groups include up to 10 patients, and family is encouraged to attend. Intervention sessions consist of 30-min of behavior change activities and 60-min focused on healthy behaviors. Sessions will be led by a health education specialist and held at local community centers. Below we outline each topic area of the SystemCHANGE™ intervention.

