## Discussion

This pilot study will represent the first randomized controlled trial to evaluate the efficacy and safety of a weight management intervention in stroke survivors using a SystemCHANGE™ intervention approach. The trial is designed to obtain effect size calculations and examine the feasibility and safety of conducting a larger clinical trial. While it will not be possible to conduct a double-blinded study, the implementation of a contact control group will help enhance retention and allow us to determine whether the actual strategies used in the SystemCHANGE™ intervention are more effective in promoting behavior change than contacts with a health education specialist. Using both self-report and objective measures of function and obtaining body composition measurements throughout the study will be important components in monitoring for potential adverse events.

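### The contact control matches the number and timing of contacts but not session time, format, peers or family, so the trial cannot, as the article says it will, determine whether the SystemCHANGE skills rather than information or contact produce an effect

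*Protocol article*

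**What the plan says.** The section Contact-control intervention makes two attribution claims, both worded as things the trial will be able to determine. The first sets the SystemCHANGE skills against simply learning the guidelines. The second asks "whether it is the skills taught in the SystemCHANGE™ intervention or simply the interactions with the health education specialist", together with the accountability that contact creates. The Discussion repeats the contact claim as a reason for having this control: it will show "whether the actual strategies used in the SystemCHANGE™ intervention are more effective in promoting behavior change than contacts" with the specialist.

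The arms are described as follows.

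- **SystemCHANGE** (section SystemCHANGE™): "12 face-to-face group sessions (1.5 h each) held weekly for 3 months", followed by booster calls. On content, "Intervention sessions consist of 30-min of behavior change activities and 60-min focused on healthy behaviors". On who is present, "Intervention groups include up to 10 patients, and family is encouraged to attend". The Diet section, one of the SystemCHANGE topic areas, adds: "Each participant will receive a personalized diet plan based on their food diary".
- **Control** (section Contact-control intervention): pamphlets on the same four topics, and telephone calls timed to coincide with the SystemCHANGE sessions. "These 20-min phone calls are intended to teach participants recommended guidelines". The SystemCHANGE skills are withheld. The number of contacts with the specialist is stated to be equivalent.

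Treatment fidelity adds that one person delivers both interventions. Potential limitations and confounders, item 2, concedes in general terms that it is difficult to tell which components of a comprehensive lifestyle intervention are effective.

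**The concern.** To isolate the skills, the control arm would have to resemble the SystemCHANGE arm in everything but the skills. By the article's own description it does not. The features that differ belong to the assigned packages and move together with arm, so randomisation does not separate them. An observed difference would be compatible with no effect of the skills at all. A null result would not separate the components either.

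Some of the unmatched features are ones the article itself regards as potentially active. The Background says that social support can help people overcome health-related barriers, and Outcomes lists social support among the potential mediators.

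What is at stake is the conclusion the trial may draw. Read as written, a positive result would be credited to the skills without evidence that they, rather than session time, group format or family, were responsible.

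**Working it through.** The article gives no figure for this claim, so there is none to reproduce. The check is a side-by-side comparison of the arms, plus arithmetic on scheduled time.

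**1. What is matched and what is not**

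| Feature | SystemCHANGE | Control | Matched? |
|---|---|---|---|
| Number and timing of contacts | 12 weekly, then boosters | same time points, then boosters | yes |
| Deliverer | one specialist | same specialist | yes |
| Broad topics | diet, activity, sleep, symptoms | same four | yes |
| Length of core contact | 90 min | 20 min | no |
| Format | face-to-face group at a community centre | telephone | no |
| Peers | groups of up to 10 | none described | no |
| Family | invited | none described | no |
| Personalised diet plan | yes | none described | no, as the text reads |

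**2. Scheduled core time** = number of contacts × minutes per contact

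- The session split is consistent: 30 + 60 = 90 min = 1.5 h.
- SystemCHANGE: 12 × 90 = 1080 min (18 h).
- Control: 12 × 20 = 240 min (4 h).
- Ratio: 1080 / 240 = 4.5. Gap: (1080 − 240) / 60 = 14 h.

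**3. The guidelines claim taken alone**

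- Healthy-behaviour part of the SystemCHANGE sessions: 12 × 60 = 720 min.
- 720 / 240 = 3, so this part alone is three times the control's whole core call time.
- Spoken guideline content is therefore unmatched even if the 30-min behaviour-change block (12 × 30 = 360 min) is set aside.

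**4. Sensitivity to the booster calls**

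The length of the boosters is not stated, and their number can be read in more than one way. Assume 1 or 3 boosters of 10 to 60 min, equal in both arms:

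- 1 call of 10 min: (1080 + 10) / (240 + 10) = 1090 / 250 = 4.36.
- 3 calls of 60 min: (1080 + 180) / (240 + 180) = 1260 / 420 = 3.0.

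Over this range the ratio stays between 3.0 and about 4.4.

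**5. What the planned analysis can separate**

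Statistical methods compares change scores between the two arms and examines within-subject change in the SystemCHANGE arm. Neither separates one component of a package from another.

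**The case against.** The strongest case on the other side has five parts.

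- **Nothing planned rests on these sentences.** The aims are effect sizes, feasibility and safety, and the central hypothesis is 5% weight loss. This stands. A reader might infer that the randomised comparison is invalid, or that a larger trial would necessarily be mis-specified. The document supports neither: the package effect is estimable, and no parameter of a larger trial can be shown to be wrong.
- **The control is better matched than a bare count of contacts.** This also stands. Timing, deliverer, broad topics, lesson plans and the existence of boosters are common to both arms.
- **The 4.5-fold ratio is session time, not specialist attention per person.** Correct. If a 90-min session were divided evenly among a full group of 10, each person would have 90 / 10 = 9 min, against a 20-min call. The direction of imbalance in individual attention is therefore unclear. It is still unmatched, so this does not rescue the contact claim. The 3-fold content ratio likewise leaves out the pamphlets. The 30/60 split is not a clean measure of skills time, because Sleep and Symptom management also teach strategies.
- **Some differences are inferred.** The diet plan is promised to each participant, but under the SystemCHANGE topic areas; the control text mentions only pamphlets and calls. Family attendance is encouraged, not required, and changing the social environment is arguably part of SystemCHANGE itself. The point holds without the diet plan. If family is counted as part of the treatment, that too favours a package-level conclusion.
- **The limitations section already concedes the issue.** Only in part. It speaks of components in general, does not name contact time, format, peers or family, and does not withdraw the two claims. As they stand, the passages conflict.

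**Conclusion.** The concern holds as a point about the stated inference. The article says the trial will determine whether skills, guidelines or contact promote healthy behaviours, and a two-arm design with these arms cannot do that. The clearest unmatched factor is scheduled core session time, 1080 against 240 min. Group versus telephone format, peers and invited family also differ by arm, as does the personalised diet plan if it is confined to SystemCHANGE.

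The conclusion rests on the arms being delivered as described. It does not depend on the diet plan or on the assumed booster length. It leaves the package-versus-package comparison, its effect sizes and the feasibility and safety aims untouched.

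**What to change.** 1. In Contact-control intervention, replace both attribution sentences with, for example: *The comparison estimates the effect of the whole SystemCHANGE package against pamphlets plus telephone-delivered information with an equal number of contacts. It cannot attribute an effect to the skills, the information or the contact.*
2. In the Discussion, soften the matching clause to the same package-level statement. It need not be deleted, since it can be read at that level.
3. In Potential limitations and confounders, item 2, add unequal contact time, format, peers and family. State whether control participants receive the personalised diet plan and, if they do not, list that as well.
4. Report contact minutes received per arm descriptively. Attendance is already tracked under Treatment fidelity; call length would need to be logged if it is not already.

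The cost is wording and a small reporting item. Arms, sample size and analysis do not change. The downside is a less ambitious stated conclusion.

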#### Booster sessions

In the SystemCHANGE™ intervention, the booster sessions will assist participants to use strategies taught in the face-to-face sessions to manage the maintenance phase of behavior change. The health education specialists will talk to patients about their efforts in self-monitoring and assist them to identify situations that are high risk for relapse. In the contact-control intervention, the booster sessions will be generic and answer questions about engaging in healthy behaviors.

#### Treatment fidelity

To promote standard application of the interventions in both the SystemCHANGE™ group and the control group, a manual of operating procedures and lesson plans outlining each session will be provided to the health education specialist and incorporated into their training. We will use the same person to deliver the interventions in both groups to facilitate standardized delivery. The health education specialist will also be given a checklist to review and use in each session and will be monitored in-person at random intervals to determine the extent to which the lesson plans are followed. Intervention fidelity will be further monitored by tracking participant attendance, monitoring completion of homework assignments, and administering quizzes to assess participants’ understanding of the material.

### Outcomes

Body fat and muscle composition will be assessed using a Bod Pod, which uses air displacement plethysmography to determine body composition [22]. Patient-reported outcomes will be the Stroke Impact Scale [23] and Reintegration to Normal Living Index [24]. Objective outcomes of health and function will be the 6-Minute Walking Test [18] and Rivermead Motor Assessment [25]. Assessors will be blinded to treatment groups.

Secondary outcomes to examine health behavior change will include a 3-day food diary, the Physical Activity and Disability Survey [26], and sleep quality measured with Neuro-QOL [27]. Fatigue, pain, anxiety, and depression will also be measured with Neuro-QOL [27]. Potential psychosocial mediators that will be measured include self-efficacy for diet [28], physical activity [29] and self-management [30], and social support for healthy behaviors [31]. Finally, assays will be performed for cholesterol, triglycerides, C-reactive protein, and hemoglobin A_1c_.

### Sample size

Our goal to recruit 35 stroke survivors is consistent with recommendations in the literature for pilot studies. Hertzog [32] has shown that samples of 10 to 20 participants per group are often adequate for evaluating feasibility in a pilot study. Furthermore, Dobkin [33] has suggested that 15 participants in each research arm are sufficient for determining whether a larger multicenter trial should be conducted.

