**Methods:**

We will conduct a randomized controlled pilot study to examine the efficacy, feasibility, and safety of the SystemCHANGE™ weight management program in overweight and obese stroke survivors. The central hypothesis of the study is that the SystemCHANGE™ intervention will help overweight and obese stroke survivors lose 5% of their body weight, thereby improving health and function. Thirty-five stroke survivors will be randomized into either the 6-month SystemCHANGE™ intervention or a contact-control intervention. Outcome measures will be assessed at baseline and again at 3 and 6 months after the interventions. Body composition will be assessed using a Bod Pod. Patient-reported outcomes will be the Stroke Impact Scale and Reintegration to Normal Living Index. Objective outcomes will include the 6-Minute Walking Test and Rivermead Motor Assessment.

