### Randomized allocation procedure

Allocation will be performed using a permuted block randomization procedure to help ensure a 1:1 ratio in each group. The allocation sequence will be determined using a computerized random number generator with block sizes of four participants. The allocation sequence will be concealed from the health education specialist and researchers who are enrolling potential participants with a sequential number of opaque sealed envelopes. Envelopes will be opened only after all pre-test data is collected. A researcher with no involvement in the delivery of the interventions or the screening of participants will prepare the envelopes.

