### Statistical methods

Recruitment and data collection efforts will be managed with Research Electronic Data Capture [34]. The first step in the analysis will be to compute summary statistics, calculate outcome scores, and conduct quality control assessments. Outcome measures will be analyzed using multivariate repeated measures or one-way ANOVAs (assuming data are normally distributed). Between-subject effects will be examined by subtracting baseline scores from post-test scores and utilizing one-way MANOVA to determine whether there are significant improvements in change scores in the SystemCHANGE™ group compared to the contract-control group. Within-subject effects will be examine with repeated-measures MANOVA comparing baseline data immediately before the SystemCHANGE™ intervention to data at 3 and 6 months after receiving the SystemCHANGE™ intervention. To help minimize missing data, we will follow recommendations by Little *et al*. [35] (for example, providing monetary incentives). Effect sizes will be calculated as Cohen’s d. Feasibility and safety of the intervention will be assessed with descriptive statistics (frequencies, percentages, means, and standard deviations): number of contacted *versus* recruited subjects, reasons for non-participation, attrition (with timing and reasons), time required to train health education specialist and arrange follow-up phone calls, and adverse event monitoring (control *versus* treatment group).

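### Efficacy is to be judged by significance tests on change scores, but 35 participants rest on pilot rules of thumb and support only preliminary estimates

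*Protocol article*

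**What the plan says.** **Size.** The Sample size section states: "Our goal to recruit 35 stroke survivors is consistent with recommendations in the literature for pilot studies". It gives two reasons, each from a cited source. The first is that "samples of 10 to 20 participants per group are often adequate for evaluating feasibility in a pilot study". The second is that "15 participants in each research arm are sufficient for determining whether a larger multicenter trial should be conducted". It states no significance level, power, standard deviation, target difference or expected precision.

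**Analysis.** Statistical methods subtracts baseline from post-test scores and compares the arms by one-way MANOVA "to determine whether there are significant improvements in change scores". Effect sizes are to be reported as Cohen's d.

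**Purpose, stated in two ways.**
- Stronger: the Abstract (Methods) describes a "randomized controlled pilot study to examine the efficacy, feasibility, and safety" of the programme. The Abstract (Discussion) and the main Discussion say the trial will evaluate efficacy and safety. The Contact-control intervention section says the investigators will be able to determine whether the taught skills, rather than learning guidelines or contact with the specialist, produce the change. The main Discussion repeats the comparison of strategies with contact.
- Softer: the last paragraph of the Background limits the pilot to preliminary estimates of efficacy and to effect size estimates. The Discussion also says: "The trial is designed to obtain effect size calculations and examine the feasibility and safety of conducting a larger clinical trial".

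**The concern.** The article gives two accounts of what the trial will conclude. The estimation account suits a pilot of this size. The testing account makes statistical significance between arms the stated mark of improvement, and nothing in the Sample size section supports that use.

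Two errors of interpretation follow if the testing account governs the report. A moderate, worthwhile benefit would more often than not come out non-significant and could be reported as no effect. A benefit that did reach significance would, on average, look larger than it is. The claim to separate the effect of skills from the effect of contact is exposed to the same problem, because it depends on the same comparison of arms.

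**Working it through.** **Inputs from the article**
- Total of 35 (Sample size).
- A "permuted block randomization procedure to help ensure a 1:1 ratio in each group", with blocks of four (Randomized allocation procedure). Eight full blocks place 16 in each arm. The remaining three assignments come from a block holding two of each, so they split 2:1. The result is 18 against 17.

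**Inputs assumed, because the article states none:** two-sided 5% level, one outcome, a two-sample t-test on that outcome, and true d from 0.2 to 1.0.

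**Step 1: the plan's own figure.** No formula leads to 35. It is consistent with the two rules: 35/2 = 17.5 lies within 10 to 20 per group, and 2 × 15 = 30 leaves 5 to spare (5/35 = 14%).

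**Step 2: power.** The noncentrality is d × √(18 × 17/35) = 2.957 × d on 33 degrees of freedom, and the critical value is t = 2.035. The last column repeats this for the 15 per arm named in the second rule.

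| True d | Power, 18 vs 17 | Power, 15 vs 15 |
|---|---|---|
| 0.2 | 9% | 8% |
| 0.5 | 30% | 26% |
| 0.8 | 63% | 56% |
| 1.0 | 82% | 75% |
| d giving 80% power | 0.98 | 1.06 |

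**Step 3: precision.** SE(d) = √(35/(18 × 17) + d²/70). At d = 0.5 this is √(0.1144 + 0.0036) = 0.343, and 1.96 × 0.343 = 0.67. The exact noncentral-t interval for an observed d of 0.5 is −0.18 to 1.17. For an observed d of 0.8 it is 0.10 to 1.48.

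**Step 4: exaggeration.** The smallest observed d that reaches significance is 2.035/2.957 = 0.69. If the true d is 0.5, every significant result in favour of the intervention therefore overstates it. In simulation such results average 0.92, and 0.92/0.5 = 1.8 times the truth.

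**Step 5: the favourable case, on weight.** Suppose the arms differed by 5 percentage points in weight change. The article gives no standard deviation, so a range is assumed. With 18 against 17, power is:
- 95% at SD 4
- 82% at SD 5
- 67% at SD 6
- 43% at SD 8

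For a 3-point difference it is 58% at SD 4 and 19% at SD 8.

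**Step 6: change scores against baseline adjustment.** Let ρ be the correlation of baseline with follow-up, and let both have the same variance σ². The change score has variance 2(1 − ρ)σ², and the baseline-adjusted outcome has residual variance (1 − ρ²)σ². Their ratio, adjusted to change, is (1 + ρ)/2, which never exceeds 1. Apart from the one degree of freedom used, adjustment is never less precise. The gain is small where ρ is near 1, as it may be for body weight.

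**The case against.** The best defence is that the article calls itself a pilot, and that its Background already uses the modest wording recommended here. That is true, and it is why this is a matter of reconciling the text and not a fault in the design. It does not remove the significance criterion in Statistical methods or the stronger claims elsewhere.

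Some stronger readings are tempting, but the document does not support them:
- *That the size is justified for feasibility alone.* The second rule concerns whether to run a larger trial. It is a go/no-go rationale, though still not a power basis for testing efficacy.
- *That the observed d will set the size of the next trial, or that a p-value will stop it.* The Discussion mentions effect sizes and a larger trial together but states no such rule.
- *That the pilot cannot show efficacy.* Effects near d = 1 are detectable, and Step 5 shows good power for a 5-point weight difference if the spread is small.
- *That safety is wrongly tested, or that zero events would be taken as proof.* Safety is described by arm, not tested, and physical function, muscle loss and other health changes are also monitored.
- *That missing intervals on d or on event percentages are a fault.* A condensed article may leave those to a fuller document.

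It is also fair to say that the power figures describe a single t-test, whereas the plan names a MANOVA. They are a guide to what 35 participants can give, not the power of the planned procedure.

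**Conclusion.** The concern holds as an inconsistency between what the trial says it will conclude and what its size supports. Between-arm significance on raw change scores is the stated efficacy criterion, and several sections promise to evaluate efficacy and identify what works. The size rests only on pilot rules of thumb, and the Background promises only preliminary estimates.

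A true d of 0.5 would be missed about 70% of the time (100% − 30%), and the interval on d is wide enough to include both no effect and a very large one. These figures rest on the assumed two-sided 5% level, one comparison and all 35 evaluable. Dropout would lower power, as would any adjustment across the several primary outcomes. The point should be acted on, because it changes what the trial may conclude and costs little to correct.

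**What to change.** 1. **Statistical methods.** Make the primary between-arm analysis the baseline-adjusted mean difference (ANCOVA on the baseline value already collected, in place of raw change scores), with a 95% confidence interval for each primary outcome. Label any p-values exploratory, and state that no efficacy conclusion will be drawn from them.
2. **Sample size.** Keep the two cited rules and add the precision that 35 participants give: about ±0.67 SD for a between-arm difference before baseline adjustment.
3. **Abstract (Methods and Discussion), Contact-control intervention, and main Discussion.** Replace the claims to examine or evaluate efficacy, and to determine whether skills or contact are responsible, with the Background's wording of preliminary estimates.

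The 5% weight-loss figure should not be presented as a target difference between arms. As written, it is a loss within the intervention arm.

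Cost: wording and a routine model. No extra patients, visits or measurements are needed. The drawback is that the stated claims become less favourable.
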